### Design and setting

This is a 12 weeks, randomized, double-blinded, placebo-controlled crossover study. From February 2013 to December 2013, Obesity Research Center of Chonbuk National University and Chonbuk National University Hospital Clinical Trial Center in Korea will participate in this study. Recruitment will therefore be expected to be completed within the study period. To recruit the participants, we will advertise in the bulletin board and on the internet homepage of Chonbuk National University. Eligible participants will be randomly allocated into 2 group (the CKJ or placebo group) with 1:1 allocation ratio and receive treatment for 12 weeks. After a 12-week washout period, the groups will be crossed over. The evaluation of participants and the analysis of the results will be performed by professional blinded to the group allocation. Written consent will be obtained from each participant before the start of this study. Our study plan is summarized in Figure 1.

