### Statistical analysis and sample size

#### Baseline data and outcomes data

Statistical analysis will be performed using SAS version 9.3 for Windows (SAS Institute, Cary, NC, USA). Data will be presented as mean values and standard deviation (SD). The Chi-square test will be performed to determine differences at baseline in frequencies of categorized variables between the groups. A linear mixed-effects model will be applied to repeated-measures data for each continuous outcome variable. Fixed effects will be included treatment group, treatment visit, and interaction between treatment group and visit. When the analysis of variance indicated significant differences among groups, post hoc test (Turkey’s test) will be used to separate the differences between groups before and after the 12-week intervention period. A value of p < 0.05 will be considered statistically significant.

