#### Sample size

Sample size calculation is performed; primary outcome measure will be the percentage body fat, whereby 1.1% is assumed a clinically relevant difference between the two groups, with a standard deviation of 2.78%, alpha set on 5% and power on 80%. This resulted in a required number of 50 subjects in each group. Assuming a dropout rate of 20%, a total of 120 subjects will be enrolled in this trial.

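### With two products the significance-gated Tukey step is redundant or costly, and no single treatment contrast is designated as the efficacy test

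*Protocol article*

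**What the plan says.** The trial has two products in a two-period crossover. Under Design and setting: "Eligible participants will be randomly allocated into 2 group (the CKJ or placebo group) with 1:1 allocation ratio", and then "After a 12-week washout period, the groups will be crossed over".

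Under Baseline data and outcomes data, each continuous outcome goes into a linear mixed-effects model: "Fixed effects will be included treatment group, treatment visit, and interaction between treatment group and visit". A conditional second step follows: "When the analysis of variance indicated significant differences among groups, post hoc test" (Tukey's, misprinted in the article) "will be used to separate the differences between groups before and after the 12-week intervention period". The threshold is given as "A value of p < 0.05 will be considered statistically significant".

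The Sample size section plans for one comparison: "primary outcome measure will be the percentage body fat, whereby 1.1% is assumed a clinically relevant difference between the two groups", with SD 2.78, alpha 5% and power 80%. It mentions no multiplicity adjustment. Table 1 schedules anthropometry at Weeks 0, 6 and 12 of each period, so every period has its own baseline.

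**The concern.** The main question is a single one: does percentage body fat at Week 12 differ between CKJ and placebo? Tukey's method protects all pairwise comparisons among three or more means, and with two products there is only one pair. The step does something only if the means compared are product-by-visit cells, which the before-and-after wording suggests. In that case the comparison of interest pays for comparisons nobody needs: before versus after within each product, CKJ versus placebo at baseline, and one product's baseline against the other's Week 12.

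The gate is a second problem. The text does not say whether significance among groups means the product main effect or the interaction. The main effect includes Week 0, before any product has been taken in that period, so it dilutes a Week 12 effect.

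At stake are agreement between the analysis and the sample size, and clarity about which result decides the trial.

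**Working it through.** **Inputs from the documents.** Difference 1.1, SD 2.78, alpha 5%, power 80%, 50 per group, 120 enrolled (Sample size); two products (Design and setting). Two-sided testing is assumed, because sidedness is not stated.

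**1. The plan's own figure.** With 1.960 + 0.842 = 2.802:
- One-sample (paired) formula: (2.78 × 2.802 / 1.1)² ≈ 50.1.
- Two parallel groups: 2 × 50.1 ≈ 100.3, so 101 per group.

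The stated 50 therefore agrees, up to rounding, with a paired calculation in which 2.78 is the SD of within-subject differences and 50 is the trial total. It does not reproduce as a parallel-group size. On either formula the test is one contrast at 1.96, with no adjustment.

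**2. Tukey over the two products only.** The critical value is the 95% studentised-range quantile for k means divided by √2. For k = 2 and large degrees of freedom it is 1.96. Power stays at 80%, so nothing is gained or lost.

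**3. Tukey over four cells (two products × Weeks 0 and 12).** The family has 6 pairs: 2 within product, 2 between products at the same visit and 2 crossed.
- Critical value for k = 4, large df: 2.57 (2.59 with 200 df).
- Per-comparison alpha: 0.010.
- Power of a contrast that has 80% at 1.96: Φ(2.802 − 2.570) = Φ(0.232) ≈ 59% (58% with 200 df).
- Sample size needed to restore 80%: ((2.570 + 0.842) / 2.802)² ≈ 1.48, about 48% more subjects.

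**4. The gate read as the product main effect, two visits.** Scale the product difference at each visit to unit SD, with expectation 0 at Week 0 and 2.802 at Week 12, and let ρ be the correlation between the two differences. The documents give no ρ; 0 to 0.9 is assumed. The averaged difference has mean 2.802 / 2 = 1.401 and SD √((1 + ρ)/2).
- ρ = 0: 1.401 / 0.707 = 1.98; pass rate Φ(1.98 − 1.96) ≈ 51%.
- ρ = 0.9: 1.401 / 0.975 = 1.44; pass rate Φ(1.44 − 1.96) ≈ 30%.

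A simulation of 400,000 draws gives the same pass rates and these joint results:

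| ρ | Main-effect gate passes | Gate, then 4-cell Tukey at Week 12 | Gate, then unadjusted Week 12 test |
|---|---|---|---|
| 0 | 51% | 42% | 49% |
| 0.5 | 37% | 35% | 36% |
| 0.9 | 30% | 30% | 30% |

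This gate therefore costs power even when the Tukey step itself costs nothing.

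**5. The gate read as the interaction.** The standardised difference in change is 2.802 / √(2(1 − ρ)). It is significant 51% of the time at ρ = 0, 80% at ρ = 0.5 and nearly always at ρ = 0.9. On this reading the gate does little harm when the correlation is high.

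**6. Absolute power under the two meanings of 2.78.**
- SD of within-subject differences, 100 completers: 1.1 / (2.78/√100) = 3.96. Power is Φ(3.96 − 1.96) ≈ 98% tested directly and Φ(3.96 − 2.57) ≈ 92% with four-cell Tukey.
- Parallel-group SD, 50 per group: 1.1 / (2.78 × √(2/50)) = 1.98. Power is about 51% tested directly and Φ(1.98 − 2.57) ≈ 28% with four-cell Tukey.

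**The case against.** The mixed model is the stated analysis and Tukey is labelled post hoc. The model contains the treatment-by-visit interaction, which with two visits is exactly the CKJ-minus-placebo difference in change, and the cell family includes CKJ versus placebo at Week 12. The sentence can also be read as comparing the two products, before and then after, at no cost in power. Tukey is conservative and does not inflate type I error. All of this stands, and it rules out several stronger readings that a reader might infer:

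- **That the trial's conclusions rest on the Tukey result.** The article does not say so.
- **That the plan tests the wrong contrasts.** The right ones are present; they are not designated.
- **That the loss is larger still because Week 6 enters the family.** Six cells would give a critical value of about 2.85 and 48% power, but the sentence names only before and after the 12-week period.
- **That a significant change under CKJ and none under placebo will count as efficacy.** The article speaks of differences between groups and nowhere makes a within-product change evidence of effect. Counselling at every visit (Table 1) is a reason to rule that inference out explicitly, not proof that it is planned.
- **That the trial is underpowered because of Tukey.** With a within-subject SD and 100 completers, four-cell power is still about 92%.

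It can also be said that choosing the decisive contrast belongs in an analysis plan that is not shown. That would answer a complaint about missing detail. Here the article states a gated rule, and that rule is at best redundant.

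**Conclusion.** The point holds in a limited form. With two products, no reading makes the gated Tukey step useful. It either repeats the ordinary test or tests cells at about 2.57 instead of 1.96, taking a nominal 80% to about 59% and departing from the sample-size comparison in which "1.1% is assumed a clinically relevant difference between the two groups". A main-effect gate would pass only about 51% to 30% of the time for an effect with 80% power at Week 12.

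The 59% rests on the four-cell reading and large degrees of freedom. The 51% to 30% rests on the main-effect reading, two visits and assumed correlations of 0 to 0.9. Both start from a nominal 80%, and actual power could be well above or below that, because the article does not say which SD 2.78 is. What does not depend on these conditions is that the step is unnecessary, its gate and family are ambiguous, and the decisive contrast is not designated.

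**What to change.** In Baseline data and outcomes data, delete the analysis-of-variance condition and the Tukey step. Name one efficacy test for percentage body fat, the outcome used for the sample size: CKJ minus placebo at Week 12 from the mixed model, adjusted for the baseline of the same period, two-sided 5%, with a 95% confidence interval. State that before-and-after changes within a product are descriptive only.

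The cost is a few sentences. The Week 0 value would enter as a covariate rather than as a level of visit, so the list of fixed effects needs a matching edit. No new visits, measurements or subjects are needed, because Table 1 already collects anthropometry at the start of both periods. The change does not settle whether the model also needs crossover terms such as period and sequence; that is a separate question.

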#### Compliance

The CKJ or placebo remaining after each visit will be quantified in order to enhance medication compliance. Subjects whose compliance with the CKJ or placebo is ≤ 70% of the total dose will be considered to have dropped-out.

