Soybeans contain various nutritious and functional components such as isoflavonoids besides soy protein which are helpful in protecting against metabolic diseases such as obesity and type 2 diabetes [9]. Fermenting soybean such as chungkookjang (CKJ) may be enhance the functionality of soybeans to protect against metabolic disease. Korean traditional CKJ is a good fermented soybean product for use as a functional food. However, traditional CKJ did not recognized as a functional food in Korea. Currently, the non-clinical data on effects of CKJ have been reported from in vivo and in vitro studies [10-18] but there is paucity the controlled clinical trials on variables of Met-S. Our previous study have revealed that traditionally made CKJ from Sunchang district of Jeolla province, Korea showed potential anti-atherosclerotic effects in overweight/obese subjects [19]. It has also been reported that traditional CKJ (made from Sunchang district of Jeolla province, Korea) improves insulinotropic action and hepatic insulin sensitivity in diabetic rats [16,17].

However, CKJ intake in Korean youth is gradually decreased due to distinctive flavor of CKJ. Therefore, the present study will be conducted by the easy-to-eat freeze-dried CKJ pills. The CKJ shows distinctive flavor characteristics. For this reason, we used cinnamon as flavoring agent to make it palatable. The purpose of this study is to evaluate the effect of CKJ compared to placebo on variables of Met-S in overweight/obese subjects.

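### Counting randomised subjects with compliance of 70% or less as dropouts selects the analysed subjects on post-randomisation behaviour, and nothing in the article keeps their data in the primary analysis

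*Protocol article*

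**What the plan says.** The rule stands in the Compliance subsection, under the heading for statistical analysis and sample size: "Subjects whose compliance with the CKJ or placebo is ≤ 70% of the total dose will be considered to have dropped-out". The sentence before it gives the source of the compliance figure and its purpose: "The CKJ or placebo remaining after each visit will be quantified in order to enhance medication compliance". Table 1 places compliance checks at weeks 6 and 12 of each period, so the figure arises after allocation.

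The subsection on baseline and outcomes data specifies a linear mixed-effects model for repeated measures. It does not say which subjects enter it.

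Under Sample size, dropouts are added on top of the required number. The section says "This resulted in a required number of 50 subjects in each group", and then "Assuming a dropout rate of 20%, a total of 120 subjects will be enrolled in this trial".

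The article names no analysis of all randomised subjects. It does not say that low compliers' measurements are kept, and it does not say whether the 70% is judged within each period or over both.

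**The concern.** A subject can attend every visit, have every measurement taken, and still be declared a dropout because of the returned product. Whether that happens may depend on the product being taken and on how the subject is doing in that period. If these subjects then leave the comparison, the analysed groups are no longer those formed by randomisation. The estimate describes subjects who complied and is not the effect of assigning CKJ.

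The crossover adds to the loss. The rule applies to either product, so failure in one period may remove the subject and with it the within-subject comparison, including measurements from the period in which the subject complied.

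At stake are the validity of the primary comparison, in either direction, and data that have been paid for and collected.

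**Working it through.** **1. The plan's own number.** Inputs from Sample size: "1.1% is assumed a clinically relevant difference between the two groups", "with a standard deviation of 2.78"%, "alpha set on 5% and power on 80"%. The paired two-sided formula gives

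n = (SD × (z₀.₉₇₅ + z₀.₈₀) / δ)² = (2.78 × 2.8016 / 1.1)² = 50.13.

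This matches the stated 50 to within rounding, but only if 2.78 is the SD of within-subject differences; 50 is then the total number of subjects. The formula for two independent groups gives 101 per group. The article then counts 2 × 50 = 100 subjects and enrols 100 × 1.2 = 120. So the required number is reached before dropout is added, and dropouts are not counted towards it. A 20% loss from 120 leaves 96.

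**2. How many subjects could be lost.** The article gives no non-compliance rates. Assume 20% in the CKJ period and 10% in the placebo period, with failure in either period removing the subject.

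| Relation between the two failures | Fraction kept | Of 120 |
|---|---|---|
| Independent | 0.8 × 0.9 = 0.72 | 86 |
| Every placebo failure is also a CKJ failure | 1 − 0.20 = 0.80 | 96 |
| No overlap | 1 − 0.20 − 0.10 = 0.70 | 84 |

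These losses come before any genuine withdrawals.

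**3. Possible bias.** Let q be the non-compliance rate in a period and g the amount by which the change in body fat is worse in a non-compliant period. The mean among all assigned is the compliers' mean plus q × g, so restricting to compliers shifts the period mean by −q × g. The CKJ − placebo difference therefore shifts by

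shift = −(q_CKJ − q_placebo) × g,

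where a negative value favours CKJ. With independent failures and a period-specific gap, the result is the same whether one period or the whole subject is removed.

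| q_CKJ | q_placebo | g (points) | Shift (points) | Share of 1.1 |
|---|---|---|---|---|
| 20% | 20% | 1.0 | 0 | 0 |
| 20% | 10% | 1.0 | −0.10 | 9% |
| 20% | 10% | 2.0 | −0.20 | 18% |
| 10% | 20% | 1.0 | +0.10 | 9%, against CKJ |

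**4. When the bias vanishes.** It is zero if the loss is equal and similarly selected on both products. It is also zero if the outcome depends only on a stable trait of the subject and whole subjects are removed: the same people then supply both periods, and the trait cancels in each within-subject difference. A simulation with 20% and 10% non-compliance driven partly by such a trait gave a mean difference of zero to within simulation error.

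**5. Consequence for the test.** Take 86 subjects and an SD of differences of 2.78. The standard error is 2.78/√86 = 0.30. With no true effect, a two-sided paired t test at 5% rejects about 6.3% of the time under a 0.10 shift and about 10% under a 0.20 shift. Power for 1.1 points, without any shift, is about 95%. If 2.78 were instead the SD of each period's value with no correlation between periods, the SD of differences would be 2.78 × √2 = 3.93, and power with 86 subjects would be about 73%.

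**The case against.** The strongest reply is that the article never says low compliers' data are deleted. They are to be considered dropouts, in a paragraph that opens with encouraging compliance, and a mixed model can keep the visits of subjects who drop out. Adding to enrolment for dropout shows that these subjects are not counted on; it does not show that they are discarded. This stands: exclusion is the natural reading but an inference. It does not remove the point, because the article states a rule and nothing in it says the data are kept.

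A reader might also infer that the rule favours CKJ, because the Background says that "CKJ intake in Korean youth is gradually decreased due to distinctive flavor of CKJ". The documents do not support that step. The Background offers the remark as the reason for using freeze-dried pills with cinnamon flavouring. The Intervention section describes a placebo of the same taste and appearance, and the trial is double-blind. Compliance could still differ for other reasons, such as tolerability, but the article gives no evidence of it, and the sign reverses if placebo loses more subjects.

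The size of the bias can also be disputed. It needs an outcome gap specific to the non-compliant period, since a stable trait cancels. The assumed shift is modest, and the 20% dropout allowance may already be meant to cover low compliers. If 2.78 is the SD of differences, power stays ample. All of this limits the severity. None of it is a reason to select the primary population on compliance.

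**Conclusion.** The point holds as a defect that should be fixed. Followed as written, the rule selects subjects on behaviour after randomisation, and the article sets no all-randomised analysis beside it. Bias is possible in either direction. It requires that poor compliance differ by product and be linked to that period's outcome, and neither is shown. Under the assumed rates and gaps the shift is 0.10 to 0.20 points, 9% to 18% of the 1.1-point target. Under equal, similarly selected loss, or a purely stable subject trait with whole-subject removal, it is zero.

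The loss of measured data is the more certain consequence if exclusion is meant. With 20% and 10% non-compliance, 84 to 96 of 120 subjects would remain (86 if failures are independent), against the 100 the plan counts on. That 86 still gives about 95% power if 2.78 is the SD of differences, so this is mainly a loss of information and of the randomised comparison.

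Two stronger conclusions go beyond the text: that measured outcomes will certainly be deleted, and that the result will be tilted towards CKJ.

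**What to change.** Replace the 70% sentence with a rule for the analysis:

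- The primary mixed model includes all randomised subjects with all available measurements, under the product assigned in each period and whatever their compliance.
- Scheduled assessments continue for subjects with low compliance.
- Compliance above 70% defines only a per-protocol set for a sensitivity analysis, and the text states whether it is judged per period or overall.

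Reporting non-compliance by product and period beside that sensitivity analysis would show whether the conditions for bias arose.

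The cost is a rewritten sentence, one extra table and continued follow-up of low compliers. The primary estimate may be smaller than one among compliers. The change should be made before data collection ends, because missed assessments cannot be recovered. It alters only who is analysed and followed, and no dose or clinical rule.

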#### Sample size

Sample size calculation is performed; primary outcome measure will be the percentage body fat, whereby 1.1% is assumed a clinically relevant difference between the two groups, with a standard deviation of 2.78%, alpha set on 5% and power on 80%. This resulted in a required number of 50 subjects in each group. Assuming a dropout rate of 20%, a total of 120 subjects will be enrolled in this trial.

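### Enrolling 120 with 20% dropout leaves 96 completers, not the 100 the plan requires, and the 50 per group can be reproduced only under an unstated meaning of the SD of 2.78

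*Protocol article*

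**What the plan says.** The Sample size section of the protocol article names percentage body fat as the outcome for the calculation. Its inputs are an effect, "1.1% is assumed a clinically relevant difference between the two groups"; a spread, "with a standard deviation of 2.78" (per cent); and error rates, "alpha set on 5% and power on 80" (per cent). The result is "This resulted in a required number of 50 subjects in each group", that is, 100 in all. The allowance for loss follows: "Assuming a dropout rate of 20%, a total of 120 subjects will be enrolled in this trial".

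Design and setting describes the trial as follows: "This is a 12 weeks, randomized, double-blinded, placebo-controlled crossover study". It adds: "After a 12-week washout period, the groups will be crossed over". Allocation is 1:1, so the two groups are the two sequence groups and every completer takes both products.

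The Sample size section does not mention the crossover. It does not say whether 2.78 is a between-subject SD, a within-subject SD or the SD of the within-subject difference, and it gives no formula or correlation. Sidedness is not stated either; the analysis section says only "A value of p < 0.05 will be considered statistically significant".

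**The concern.** There are two separate problems in the same short paragraph.

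First, the enrolment target does not meet the requirement it was derived from. If the assumed dropout occurs, fewer than 50 per group finish.

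Second, the calculation is worded as a comparison of two groups, but the trial is a crossover. The usual formulae for those two designs, applied to the same four inputs, give totals that differ about fourfold. Because 2.78 is not labelled, a reader cannot tell which calculation was done, and so cannot tell what power the trial has for a 1.1-point difference. The claimed 80% is the yardstick for reading a null result, so it should be reproducible and should refer to the number of subjects expected to finish.

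**Working it through.** **Inputs** (protocol article, Sample size): difference d = 1.1; SD s = 2.78; alpha 0.05; power 0.80; 20% dropout; 120 enrolled. Two-sided testing is assumed, because the article does not state sidedness.

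Common factor: (1.96 + 0.8416)² x (2.78/1.1)² = 50.13.

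**1. Reproducing the plan's 50 per group.** In a two-period, two-sequence crossover with s as the within-subject SD, the variance of a subject's treatment difference is 2s². The number per sequence is then (z_alpha + z_beta)² s²/d² = 50.13, or 100.26 in total. This matches the stated 50 per group; rounded up it is 51. The result does not depend on the between-subject variance, so it holds at any correlation between periods.

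**2. The same inputs under other meanings of 2.78.**

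| Meaning of 2.78 | Formula | Required |
|---|---|---|
| Within-subject SD, crossover | 50.13 per sequence | 101 in total by z (102 for equal sequences) |
| SD of the within-subject difference, crossover | 50.13 in total | 51 (z) to 53 (t) in total |
| SD in each of two independent groups | 2 x 50.13 = 100.26 per group | 101 (z) to 102 (t) per group, 202–204 in total |

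One-sided testing does not rescue the two-group reading: it gives 79 per group by z.

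**3. Dropout.**
- Plan: 100 x (1 + 0.20) = 120.
- Needed to retain 100: 100/(1 − 0.20) = 125, or 126 for two equal groups of 63.
- Left from 120 after 20% loss: 120 x 0.80 = 96, or 48 per group.
- The loss that 120 can absorb while keeping 100: 20/120 = 16.7%.

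**4. Power for d = 1.1.**

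Within-subject SD, N completers: Φ(d/(s√(2/N)) − 1.96).
- N = 100: 1.1/(2.78 x 0.1414) = 2.798, giving 79.9% by z and 79.1% by t.
- N = 96: 1.1/(2.78 x 0.1443) = 2.741, giving 78.3% by z and 77.4% by t.

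SD of the within-subject difference: Φ(d√N/s − 1.96).
- N = 96: 97.2% by z, 97.0% by t.
- N = 100: 97.7% by z, 97.5% by t.

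Two independent groups of n: Φ(d/(s√(2/n)) − 1.96).
- n = 50: 50.7% by z, 50.0% by t.
- n = 48: 49.1% by z, 48.4% by t.

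**The case against.** The strongest defence is that the plan's figure is right for its design. The article makes the trial a crossover, its groups are sequence groups, and the standard crossover formula with a within-subject SD returns 50 per sequence. This stands. A reader might infer that 50 per group simply does not follow from the inputs. The documents do not support that.

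A reader might also infer that the trial has only about a 50% chance of detecting its target effect. That figure needs 50 observations per treatment, which means discarding the second period. Under Design and setting every completer receives both products, so 100 completers give about 100 observations on each. The analysis section specifies a linear mixed-effects model for repeated measures, not a two-sample test. The 50% therefore shows what the paragraph's wording would imply if taken literally; it is not the power of the planned trial.

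Nor does 80% power at 100 completers require the two periods to be uncorrelated. That condition arises only if 2.78 is a single-period SD. With a within-subject SD, the correlation between periods does not enter.

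Finally, a journal article condenses a full protocol, and the type of SD and the formula are details that may appear there. That limits the weight of the missing label taken alone. It does not excuse wording that describes a different design, and it does not touch the dropout step, which is stated in full in the article and is wrong under every reading. The defence is right that the cost of the dropout error is small: 1.6 to 1.7 percentage points of power on the within-subject reading.

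**Conclusion.** The dropout error is certain and needs no assumption about the SD: 120 enrolled with 20% loss gives 96 completers, four short of the plan's own 100.

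The 50 per group is reproducible (50.13, strictly 51), but only if 2.78 is a within-subject SD in a crossover. A single-period SD with uncorrelated periods is a special case of this. The paragraph does not say so, and its two-group wording points elsewhere. Depending on the label, the inputs support a required total from about 51–53 up to 202–204.

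With two-sided testing at 5%, power at the expected 96 completers is about 77% (t) or 78% (z) if 2.78 is the within-subject SD, and about 97% if it is the SD of the within-subject difference. The first falls slightly short of the claimed 80%; the second exceeds it comfortably. The defect is that the stated size and power do not match what the plan delivers. It does not make the trial grossly underpowered.

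**What to change.** Keep 120 and rewrite the Sample size paragraph as a crossover calculation:

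- State what 2.78 is: the within-subject SD, the SD of the within-subject difference, or a single-period SD with an assumed correlation between periods. Name the formula and the sidedness.
- Replace the two-group wording with the treatment difference within the crossover. Give the required number as total completers, or as a number per sequence named as such.
- Correct the dropout step. Say that 120 enrolled with 20% loss leaves 96 completers, and replace the claimed 80% by the power at 96: about 77% (t) or 78% (z) on the within-subject reading, about 97% on the SD-of-difference reading.

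This changes one paragraph and adds no participants. The downside is that, on the within-subject reading, the stated power becomes slightly less favourable. If the sponsor would rather retain 100 completers, enrolment has to be 125, or 126 for equal groups.
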